**Methods:**

A non-inferiority randomized clinical trial with two parallels arms (1:1) will be conducted. Children with 4 to 8 years will be selected at Clinic of Pediatric Dentistry at Ibirapuera University. 108 teeth will be randomized into two groups: (1) Calcium hydroxide cement associated with HVGIC and (2) HVGIC restoration. Primary outcome will be considered the pulp vitality and to be evaluated after 6, 12, 18 and 24 months by two calibrated examiners. Survival of restorations will also be evaluated in the equal intervals. The duration of dentals treatment and the cost of all materials used will be considered for estimating of cost-efficacy of each treatment. Individual discomfort will be measured after each dental procedure using the Wong-Baker’s Facial Scale. For the primary outcome, Kaplan-Meier survival and the long-rank test will be used to comparison between the groups. Cox regression will be performed to assess the influence of variables on the outcome. For all analyzes, the significance level is set at 5%.

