Nevertheless, the high viscosity glass ionomer cement (HVGIC), which has been the material of choice for medium and low deep cavities in Atraumatic Restorative Treatment (ART), has not been considered in the studies that focusing in treatment of deep caries lesion [14]. Using this material in pediatric dentistry seems to be an alternative to decrease the time required for the clinical care, due to the facility to perform the restorations with HVGIC. Considering the philosophy of ART, it will be possible to restore the deep caries lesion with pulp vitality without the use of rubber dam and anesthesia. However, to date, there are no well-designed clinical trials evaluating cost-efficacy as well as other important patient-centered outcomes of the treatment of deep caries lesions with HVGIC.

Thus, this study aims as primary outcome to compare the pulp vitality of two types of treatment for deep caries lesions in primary molars (HVGIC restoration and restoration with calcium hydroxide cement associated with HVGIC) by a non-inferiority randomized clinical trial with two parallel arms. The secondary outcomes will compare the survival of restorations, caries progression, cost-efficacy and discomfort between the two treatment options. Our hypothesis is that the dental pulp vitality of teeth restored with HVGIC do not differ from teeth restored with a pulp capping material.

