### Sample size calculation and selection

Participants will be selected with ages ranging from 4 to 8 years searching for dental treatment, coming from the Clinic of Pediatric Dentistry of the Ibirapuera University, Sao Paulo, Brazil. The screening will be carried out under natural light with the aid of a wooden spatula. Children with potential for inclusion in the research will be referred for clinical examination. Children with at least one primary molar with deep cavitated caries lesion on the occlusal or occlusoproximal surfaces will be included.

Special needs patients using orthodontic appliance and / or systemic diseases that may influence the oral cavity, will be excluded. In addition, teeth with pulp exposure, spontaneous pain, mobility, abscess or fistula near the tooth, teeth with restorations, sealants or defects of enamel formation will be excluded.

Initial periapical radiography will also be performed to confirm the depth of the lesions as well as to exclude a possible pulpal involvement – presence of radiographically visible furca/periapical lesion - linked to clinical evaluation by PUFA index [15] - presence of ulceration, fistula and abscess, reported pain and pathological mobility. It will be considered as deep caries lesion those that will be located in the inner third of dentin.

To perform the sample size calculation, the expected success rates of pulp vitality using a calcium hydroxide cement as pulp capping material was considered 94% in 12–29 months [16]. It was considered that a clinically significant difference was 15% in the success rate between the groups. Therefore, considering a significance level of 0.05 and a power of 0.80, using a one-tailed test for non-inferiority studies, with a 20% increase due to a possible sample loss and 40% by cluster of more than one tooth per children, we reached the final rounded number of 54 teeth per group, resulting in 108 teeth in total [17].

Recruitment are taking place from November 2016 to April 2018. After allocation and treatment in one of the groups, with mean of 1 month per participant, these will be followed up for 24 months. Figure 1 displays the flow diagram of clinical trial’s phases.

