##### Data analysis

The efficacy of each treatment will be assessed by five main outcomes:Success rate of pulp vitality (Primary outcome) andsurvival of restorations (secondary outcome): Kaplan-Meier survival and the Long-rank test will be used to compare the success rates between the experimental and control groups. Cox regression model with a shared frailty will be performed in order to allow the evaluation of the influence of the variables in the results.Progression of deep caries lesions (secondary outcome): Qui-square test will be used to compare this outcome between the groups.Cost-efficacy (secondary outcome): Incremental cost-efficacy ratio will be calculated considering the ratio between the total cost of each treatment and the success rate after 2 years.Self-reported discomfort (secondary outcome): Poisson regression will be used to compare both groups and to asses of the influence of other variables on this outcome.

For all analyzes, the significance value will be adjusted to 5%.

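### The trial is sized on a one-tailed 5% non-inferiority test, but the analysis section applies an undivided 5% to a log-rank test and a Cox model and carries neither the one-tailed level nor the 15 points into the primary comparison

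*Protocol article*

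**What the plan says.** All references are to the protocol article.

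- **Sample size calculation and selection.** The control rate is given as follows: "the expected success rates of pulp vitality using a calcium hydroxide cement as pulp capping material was considered 94% in 12–29 months". The difference is given as "It was considered that a clinically significant difference was 15% in the success rate between the groups". The error rates are fixed by "considering a significance level of 0.05 and a power of 0.80, using a one-tailed test for non-inferiority studies". After a 20% increase for loss and 40% for clustering of teeth within child, the result is 54 teeth per group, 108 in total.
- **Data analysis.** Pulp vitality, the primary outcome, is compared between groups by Kaplan-Meier and log-rank methods, with a shared-frailty Cox model for the influence of other variables. One level covers everything: "For all analyzes, the significance value will be adjusted to 5" per cent. The Methods part of the Abstract repeats it: "For all analyzes, the significance level is set at 5" per cent.
- **Background.** The hypothesis is put as equality: "Our hypothesis is that the dental pulp vitality of teeth restored with HVGIC do not differ from teeth restored with a pulp capping material".

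The sidedness of the test is stated only in the sample size section. The 15 points also appear only there.

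**The concern.** A non-inferiority conclusion depends on three things fixed together: the margin, the one-sided level (equivalently, which confidence interval decides), and the sample size that gives adequate power at that level. The sample size section sets all three. The analysis section sets a level for every analysis and names the primary test, but the test it names is one of equality between survival curves, and the level has no side attached. Carried out as written, that section would not perform the test for which the 108 teeth were calculated.

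Two analysts could follow this text in good faith and use different rules. One would take the lower limit of a 90% interval, matching the one-tailed 5% used for sizing. The other would take a 95% interval, the usual companion of an unqualified 5%, which tests against the 15 points at one-sided 2.5%. The same data could then be reported as non-inferior or not, and the power for the same 54 teeth per group differs between the two rules.

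**Working it through.** **Inputs**

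- Control success 94%, difference 15 points, level 0.05 one-tailed, power 0.80, allowances of 20% and 40%, 54 teeth per group: all from Sample size calculation and selection.
- 94% success in the experimental arm as well: my assumption, in line with the hypothesis of no difference in Background.
- The 15 points read as the non-inferiority margin. Reading them as a superiority contrast of 94% against 79% needs 64 (one-sided) or 81 (two-sided) teeth per arm before inflation, which does not lead to 54 per group.

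**Step 1: reproduce the plan's figure**

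n per arm = 2 × 0.94 × 0.06 × (1.645 + 0.842)² / 0.15² = 31.0

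Inflation: 31 × 1.2 × 1.4 = 52.1. Rounding up at each step gives 38, then 54. Dividing by 0.8 for loss gives 31 / 0.8 × 1.4 = 54.25. The stated 54 therefore reproduces at one-tailed 5%.

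**Step 2: the same formula at one-sided 2.5%**

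With 1.96 in place of 1.645, n = 39.3, so 40 per arm before inflation. That is 40 × 1.2 × 1.4 = 67.2 to 40 / 0.8 × 1.4 = 70 after it. The 54 per group comes only from the one-tailed 5% level.

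**Step 3: power of the planned size under each rule**

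Undoing the allowances gives 54 × 0.8 / 1.4 = 30.9 or 54 / 1.2 / 1.4 = 32.1 effective teeth per arm, so 31 to 32.

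Power = Φ(0.15 / SE − z), with SE = √(2 × 0.94 × 0.06 / n). At n = 31, SE = 0.0603 and 0.15 / SE = 2.487.

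| Effective teeth per arm | One-sided 5% (90% CI decides) | One-sided 2.5% (95% CI decides) |
|---|---|---|
| 31 | 80.0% | 70.1% |
| 32 | 81.1% | 71.4% |
| 54 (no loss, no clustering) | 94.9% | 90.7% |

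**Step 4: where the two rules part**

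With the formula's SE of 6.03 points at n = 31, the observed difference must exceed −15 + 1.645 × 6.03 = −5.1 points under the 90% rule, and −15 + 1.96 × 6.03 = −3.2 points under the 95% rule. A result between −5.1 and −3.2 points passes one and fails the other.

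**Side note: quality of the normal approximation**

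Exact binomial enumeration, with power at 94% in both arms and error at 94% against 79%, shows that the formula is optimistic at this size.

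- An unpooled Wald test at nominal one-sided 5% has exact error 7.4% at n = 31 and 7.0% at n = 32. It is 6.5% at 30, 6.3% at 33 and 6.0% at 54. At n = 31 it runs from 5.5% to 9.9% for control rates of 85% to 98%.
- A score test at one-sided 5% has exact error 5.5% and power 73% at n = 31; its power is 65% to 73% for n = 30 to 33. At one-sided 2.5% its power is 49% at n = 31 and 57% at n = 32.

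**The case against.** The strongest reply is that nothing is contradicted. The figure is 5% everywhere, no section calls the primary test two-sided, and no section mentions a 95% interval or 2.5%. Read as a whole, the sample size section supplies the missing side, and on that reading the stated 80% reproduces. This stands: a reader might infer that the plan is analysed two-sided and that its real power is therefore 70%, but the text does not say so. Log-rank and chi-square tests are non-directional by convention, and the hypothesis is worded as equality, so the two-sided reading is natural. It remains a reading.

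A reader might also infer from the exact calculation that the plan has a true error rate of 7.4%. The documents do not support that. A sample-size formula has no type I error; a test does, and the plan names no Wald test. The 7.4% belongs to one test at exactly 31 independent teeth per arm and a 94% control rate.

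Nor do the documents support dropping the 40% cluster allowance to recover power. The plan adopts it explicitly because a child may contribute more than one tooth.

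Finally, the method for the interval may properly be left to a statistical analysis plan. That is fair for the choice of method. It does not dispose of the point, because the article does not defer on the level or the test: it fixes a level for all analyses and a primary test, and these do not match the test used for sizing.

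**Conclusion.** The point holds as an inconsistency of specification. The one-tailed 5% level and the 15 points that produced 54 teeth per group are not carried into the primary comparison, so the plan does not say which interval decides non-inferiority. No stated figure is miscalculated.

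The consequence is conditional. If a 95% interval decides, power by the plan's own formula is about 70% rather than 80%, at 31 effective teeth per arm (71% at 32). This assumes 94% success in both arms and that the loss and cluster allowances are fully used. If they were not needed at all, power would be 91% even under the stricter rule. The approximation matters only to how power is quoted: if a score-type interval is used, about 73% at one-sided 5% is nearer than 80%.

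**What to change.** In Data analysis, state that:

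- the primary non-inferiority comparison is one-sided at 5%;
- non-inferiority is concluded if the lower limit of the two-sided 90% confidence interval for the 24-month difference in pulp-vitality success (HVGIC minus control) is above −15 points, with allowance for clustering of teeth within child;
- all other tests are two-sided at 5%.

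Make the sentence on the level in the Abstract agree.

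If a 95% interval is to decide instead, restate the power in Sample size calculation and selection as about 70% by the plan's formula. If a score-type interval is chosen, quote power on that basis: about 73% at one-sided 5% (65% to 73% for 30 to 33 effective teeth), or 49% to 57% at one-sided 2.5% for 31 to 32.

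The cost is a few sentences and possibly a less favourable power figure. No extra teeth are needed.

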### Patient and public involvement

Children treated by ART philosophy have pointed for less anxiety, pain and discomfort with minimally invasive techniques, as previously studies showed [21]. Thus, this preference reported by them helped to guide this trial. The research question emerged from the lack of evidence of the use of ART philosophy for deep cavitated caries lesions in primary molars, both for efficacy, as well as the discomfort caused to patients.

Because it is a clinical study methodology, the patients are still being involved in the recruitment, conduction and evaluation of the study. However, there is no involvement of patients or public in trial design.

The authors intend to disseminate the results of the present study not only through scientific publications, but also with public and private clinicians.

### Ethics and dissemination plain

This clinical trial was approved by the local ethical board committee from the Faculty of Dentistry of the Ibirapuera University (registration no. 1.670.059). Participants will be included after their legal guardians have signed an informed consent form containing detailed information about the research and the children nod their participation. The data from participants’ individual information will be grouped in order to prevent individual participant identification and then will be published in a peer-reviewed journals and presented at conferences.

## Discussion

Studies focusing in smart and comfortable techniques to children’s treatment should be conducted in order to guide the dentists to use of friendly-patient approaches. Thus, this is the first clinical trial that will evaluate as primary outcome the success rate considering the pulp vitality between restoration with calcium hydroxide cement associated with HVGIC and HVGIC restoration for treatment of deep caries lesions in primary molars in according the philosophy of ART.

The evaluation of this outcome will take into account clinical signs associated with symptoms, since that the most of the previous studies considering the survival of restoration as the primary outcome and not pondering the pulp condition. However, the main reason to use the pulp capping material is to protect the pulp tissue. Thus, it should be considered in the evaluation.

Others secondary outcomes will be considered. The choice of outcome measures was based on the efficacy of the treatment, but also in patient-centered outcomes, thinking in about the practice-based evidence where the preference of patient should be englobed in the treatment choice. Analysis of cost will be also performed in order to project the incremental cost of the treatments with higher failure rate for the public health manager.

This is important to highlighted that it will not be possible the blinding of the operators because of the evident differences between the both techniques. Nevertheless, to minimize this situation, the allocation of the treatments will be only performer after the selective caries removal. Furthermore, the patient and examiner can be considered as blinded.

Thus, our study desires to answer if it is possible to restore deep caries lesion of primary teeth only with HVGIC considering the ART philosophy. Since that this hypothesis was sustained, the pediatric dentistry can be used a friendlier technique to deep caries lesion management.

## Abbreviation

ART: Atraumatic Restorative Treatment
HVGIC: High viscosity glass ionomer cement
